**Fig. 2 Fig2:**
[figure not shown]
Schedule of assessments and procedures

### Randomization and intervention

#### Prolonged Exposure (PE)

All veterans receive individual sessions of Prolonged Exposure therapy for PTSD (PE). PE consists of up to 12 sessions delivered once weekly for 60 to 90 min. Foa’s PE protocol is used, given consensus statements regarding its efficacy for PTSD as well as its wide-scale dissemination [21]. Consistent with the manual guidelines, sessions consist of imaginal (in session) exposure exercises, in-vivo (out-of-session) exposure exercises, review of homework, and relevant processing of in- and out-of-session activities. Study therapists were trained and certified through the VA’s PE certification process and they receive weekly supervision for all cases. Veterans in the RESCUE + PE and CI + PE conditions receive additional psycho-educational materials relevant to either canine shelter volunteering or community agency volunteering, respectively. Discussion regarding experiences with assigned volunteer activities is incorporated into treatment sessions, generally during discussion of homework assignments and homework review. Thus, the control condition matches the experimental condition in relation to both the addition of out-of-session volunteer activities and in-session discussion and processing of those activities.

#### Recovery through Engagement with Shelter Canines, Understanding, and Exposure (RESCUE)

Half of all veterans are randomly assigned to receive RESCUE concomitant with PE. RESCUE volunteer sessions occur once weekly at an area Society for the Prevention of Cruelty to Animals (SPCA) chosen by the veteran and last approximately 90 min. Expectations regarding volunteer assignments are reviewed by study staff prior to the start of treatment and progress or difficulties with the assignments are discussed throughout treatment as described above. Prior to starting their volunteer assignment, participants receive an orientation by SPCA professionals consistent with what is provided to community volunteers. This training includes an orientation to the physical space of the shelter, basic safety and handling education, and discussion of daily tasks involving interaction with the canines that can be accomplished. Participants are limited to working with *non-aggressive* dogs.

#### Community Involvement volunteer condition

Half of all veterans are randomly assigned to participate in Community Involvement concomitant with PE. Veterans are provided with a brief handout listing local community agencies that are actively recruiting or accepting volunteers (e.g., local Young Men’s Christian Association (YMCA) facilities, soup kitchens, housing and community improvement projects, reading partners) but they are also encouraged to choose any agency not listed on the study handout if they prefer. Veterans are specifically instructed to not volunteer at an animal shelter. Veterans are responsible for calling the volunteer agency of their choice and setting up an initial orientation with the facility. They are also asked to engage with the agency at least once per week for the duration of treatment. Study staff are available to help participants coordinate the logistics of initiating and maintaining contact with their chosen community agency as needed. Comparable to the RESCUE condition, study therapists review progress and/or difficulties with the volunteer assignments throughout treatment as part of the homework assignment and review process.

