## Background

Prolonged Exposure (PE) is considered an evidence-based treatment (EBT) for PTSD [1, 2] and has been widely disseminated throughout Department of Defense (DoD) and Veterans Affairs (VA) treatment facilities. Although up to 80% of patients demonstrate clinically meaningful improvement after completing an EBT for PTSD such as PE [1–3], a significant number of individuals do not initiate PTSD treatment or drop out of treatment prematurely (as high as 78% and 36% overall pooled dropout rates across studies) [4–7]. Given the wide-scale availability of PE and other EBTs for PTSD in VA and DoD treatment settings, and the robust effect sizes for treatment completers, there is a need for novel methods that can improve PTSD treatment engagement and decrease attrition.

One potential avenue for improving EBTs for PTSD is by targeting PTSD symptoms that may adversely impact treatment engagement early in the treatment process. Emotional numbing is part of the symptom profile of PTSD and consists of symptoms that reflect difficulties in experiencing positive emotions such as love and happiness, loss of interest in activities that were previously important or pleasurable, and feeling distant and cut off from others. In relation to PTSD and other psychiatric disorders, emotional numbing is also associated with apathy and low motivation [8, 9]. Together, these symptoms can limit an individual’s ability and willingness to engage in treatment [10, 11], particularly a treatment that encourages connecting emotionally with trauma-related material. Consistent with this, poor response to PE has been associated with blunted emotional reactivity to trauma cues early in therapy [12].

A promising mechanism for decreasing emotional numbing is through therapeutic human-animal interaction (HAI [13–15]). HAI refers to the purposeful and semistructured social pairing of a human with a domesticated animal for therapeutic purposes. A number of diverse studies have found that HAI can have positive effects on emotional and physical functioning, stress reactivity, and social functioning [16–18]; and among those with psychiatric symptoms, HAI interventions have been found to improve depression, anxiety, and PTSD [16, 19, 20]. Although promising, the HAI literature is tempered by methodological limitations, such as difficult-to-replicate study procedures, over-reliance on self-report measures, and lack of adequate controls/randomization (e.g., [18–20]).

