### Randomization procedures

Once eligibility is established, veterans are assigned 1:1 to one of the two treatment groups by the Project Coordinator using a web-based computer-generated randomization scheme. Once a veteran is randomized and attends the first session, they are entered into the study and included in the intent-to-treat (ITT) analysis. The post-treatment assessors (12- and 3-month assessors) will be blinded to condition. The Principal Investigator (PI) (for clinical oversight/supervision) and Project Coordinator (for randomization/regulatory reasons) will not be blinded to treatment condition. The study therapists likewise will not be blinded because discussion of volunteer assignments is part of the treatment protocol. It is not anticipated that the post-treatment assessors will need to be unblinded as this will be their only point of contact with the study participant. If the blind is accidentally broken, the Clinician Administered PTSD Scale (described below) will be reviewed by another team member for fidelity and evaluated against the PTSD Symptom Checklist (described below) which is self-report.

Inclusion criteria for the study are as follows: (1) *Diagnostic and Statistical Manual for Mental Disorders, version 5* (DSM-V) PTSD diagnosis (via the Clinician Administered PTSD Scale; CAPS [22];) stemming from a duty-related Criterion A event [23]; (2) male or female aged 18 to 64 years.

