Exclusion criteria for the study are as follows: (1) presence of an active substance-use disorder that requires medical detoxification; (2) diagnosis of Antisocial Personality Disorder or history of animal cruelty; (3) presence of delirium, dementia, amnestic disorders, or other cognitive disorders and psychotic disorders that would likely interfere with the ability to consent or comply with study procedures; (4) presence of active/uncontrolled bipolar I or II disorder; (5) current use of benzodiazepine medications (if willing, participants are required to taper and cease use under physician supervision, and they must be off the medication(s) for at least 2 weeks prior to enrolling in the study); (6) recent prescription of an SSRI antidepressant medication or a recent change in dosing (participants must be on a consistent dose for at least 2 weeks prior to enrollment and throughout the study); (7) suicidal or homicidal ideation with intent; (8) lack of English language fluency; and (9) presence of a specific phobia related to dogs or any other relevant aversion to dogs (i.e., allergy). Once enrolled, participants will only be discontinued from the study if the study appears to be causing them undue or atypical distress and/or if the patient elects to terminate their study participation.

See description of instruments below under the “Assessment measures” section and Fig. 2 for the study assessments and procedures.

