### Assessment measures

Participants are screened for eligibility by the Project Coordinator who has a master’s degree in counseling psychology. This screening/baseline assessment includes informed consent and administration of a battery of measures consisting of the Clinician Administered PTSD Scale-5 (CAPS [22];), the Structured Clinical Interview for DSM-IV Axis I Disorders (SCID-IV) Modules for Mood and Generalized Anxiety [24]; Clinical Global Impressions (CGI [25];); Digit-Span [26]; and a Medication Tracking Measure. Self-Report measures include the Posttraumatic Stress Disorder Checklist (PCL-5 [27];); Beck Anxiety Inventory (BAI [28];); Patient Health Questionnaire (PHQ-9 [29];); Quality of Life Index (QLI [30];); World Health Organization Disability Assessment Schedule II (WHODAS II [31];; Emotional Reactivity and Numbing Scale (ENRS [32];); a study-specific Previous Experience with Dogs Form; Deployment Risk and Resilience Inventory (DRRI-2 [33];). The baseline assessment typically occurs over one to two sessions and veterans are compensated US$50.00 for their time.

Weekly treatment session measures include the PCL-5; Utilization of Treatment Inventory (UTI, weekly [21];), a study-specific Community Involvement Report Form, and a study-specific Violations of Expectancies about Imaginal Exposure Form (VEMIE; sessions 2, 3, and 4). At mid-treatment veterans complete the BAI; PHQ-9; Medication Tracking Measure; and Client Satisfaction Questionnaire – 8 (CSQ-8 [34];).

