A strength of the proposed project is that it is designed to target the significant number of veterans and active duty personnel with PTSD who are at risk for refusing or dropping out of EBTs [4, 5, 7, 37]. Additionally, RESCUE incorporates HAI into the chronological treatment progression of PE by taking advantage of an already existing and disseminated infrastructure related to (1) volunteering at an SPCA to socialize shelter dogs for eventual adoption and (2) standard PTSD treatment guidelines (i.e., in-vivo exposures) as mandated by the Uniform Mental Health Services Handbook (VHA HANDBOOK 1160.01). By taking advantage of the availability of SPCA shelters nationally as well as existing service delivery models for PTSD, RESCUE can easily be scaled up for wide-scale implementation and dissemination. Further, the theory-driven mixed quantitative/qualitative methods design of this trial will allow for a better understanding of how HAI may be beneficial for individuals with PTSD as well as provide information on how to further improve the treatment program moving forward. Altogether, this study should provide timely information regarding incorporating HAI into EBTs for PTSD.

A significant contribution of the current study is in relation to specifying an ecologically valid, active, and well-matched control condition designed to determine animal-specific or HAI-specific effects. Additionally, much of the extant literature to date has focused on the beneficial health effects of HAI through long-term pet ownership rather than the effects of specific interventions. Finally, reviews of HAI specifically related to therapeutic interventions or specific clinical populations suggest an overall lack of methodological rigor [16, 18–20] which is a considerable barrier to progress in the field. The current study team noted these trends when designing the trial and decidedly erred on the conservative side in relation to specifying the control group. The control group is well matched in and outside of treatment sessions and participants are randomly assigned to conditions. Additionally, the experimental condition is not related to receiving additional services or a service dog, and therapy is provided using an ecologically valid treatment setting and referral stream.

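### The control arm is barred only from animal shelters, so a control veteran can follow the instruction exactly and still volunteer with animals

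*Protocol article*

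**What the plan says.** The Discussion describes a "well-matched control condition designed to determine animal-specific or HAI-specific effects". The Background supplies the construct: "HAI refers to the purposeful and semistructured social pairing of a human with a domesticated animal for therapeutic purposes".

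The control activity is set out in the Protocol article under Community Involvement volunteer condition. Veterans get a handout of local agencies, and "they are also encouraged to choose any agency not listed on the study handout if they prefer". The next sentence is the only restriction on the choice: "Veterans are specifically instructed to not volunteer at an animal shelter". The handout examples given are a YMCA, soup kitchens, housing and community improvement projects, and reading partners. None is an animal agency.

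Volunteer activity is followed during treatment. Therapists discuss it with the homework in both arms (Prolonged Exposure section), and a Community Involvement Report Form is completed weekly (Assessment measures). The article does not describe what that form records.

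**The concern.** The comparison is informative about HAI only if the two volunteer activities differ in animal contact. The authors saw that this needed a rule and wrote one, but it names a type of site, not the exposure. Because veterans are also encouraged to look beyond the handout, non-shelter animal roles remain open to them.

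At stake is the size of the observable difference. Animal contact in the control arm shrinks it. The Discussion already grants that a negative result will be harder to interpret than a positive one, and unrecognised animal contact among controls would add a further explanation for such a result. The limitation it acknowledges about self-selected control activities covers preference, comfort and ease of scheduling, but not animal contact.

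**Working it through.** **1. Scope of the rule against scope of the construct**

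| Element | Defined by | Section |
|---|---|---|
| HAI | Contact with a domesticated animal, purposeful and semistructured, with therapeutic intent | Background |
| Purpose of the control | Showing animal- or HAI-specific effects | Discussion |
| Permitted control activity | Any agency, on or off the handout | Community Involvement volunteer condition |
| Barred control activity | Animal shelters only | Same |

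A riding programme or a service-dog charity passes the last two rows and still involves a domesticated animal. These two examples are mine; the article names neither. Control volunteering also serves as in-vivo exposure work and is processed in therapy, as in the RESCUE arm. An animal role in the control arm would therefore sit in much the same therapeutic frame.

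**2. The plan's own figure**

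The sample size section states 85% power for 0.3 SD with 35 per arm, three time points, intra-class correlation up to 0.5 and two-sided 0.05. For the mean of three measures at correlation 0.5:

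- variance factor = (1 + 2 × 0.5)/3 = 0.667
- standard error = √(2 × 0.667/35) = 0.195 SD
- 0.30/0.195 = 1.54
- power = Φ(1.54 − 1.96) ≈ 34%

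The stated 85% is not reproduced on this reading. That is a separate matter, and the present point does not rest on it. The 0.30 SD serves below only as a reference effect.

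**3. Dilution**

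Let p be the share of controls who take up an animal role after randomisation, and r the share of the RESCUE effect that they obtain. The documents give neither, so both are assumed. The observed difference is 0.30 × (1 − p × r).

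| p | Controls affected (p × 35) | r = 1 (upper bound) | r = 0.5 |
|---|---|---|---|
| 10% | 3.5 | 0.27 SD | 0.285 SD |
| 20% | 7 | 0.24 SD | 0.27 SD |
| 30% | 10.5 | 0.21 SD | 0.255 SD |

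**4. Effect on power at r = 1**

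Taking the stated 85% at face value, power = Φ((1.960 + 1.036) × (1 − p) − 1.960). This gives 76.9%, 66.9% and 55.5% for p of 10%, 20% and 30%. Starting from the roughly 34% of step 2, the corresponding values are 28.2%, 23.3% and 18.8%.

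**The case against.** The strongest reply is that contamination is hypothetical. The article reports no case and no rate, and every handout example is free of animals. One sentence in an article may also condense fuller participant instructions. This stands as a limit on weight. However, the rule as printed is explicit and paired with free choice of agency, so the point concerns what the article states and not something it leaves out.

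A second reply is that ordinary animal contact is not RESCUE. The experimental arm has shelter orientation, canine-specific materials and weekly sessions of about 90 minutes, and the definition of HAI asks for purposeful, semistructured pairing. This also stands. It is why the r = 1 column is an upper bound for each p.

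A third is that the weekly form and the therapists' review would bring animal contact to light. They may well do so. But they do not prevent it, and nothing in the article makes a non-shelter animal role a departure from protocol.

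Finally, dilution runs toward no difference and so would not by itself produce a spurious benefit. That is correct; the cost falls on sensitivity and on the reading of a null result.

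A reader might go further and infer that the entry criteria are also at fault. The animal-related exclusions cover only "diagnosis of Antisocial Personality Disorder or history of animal cruelty" and dog phobia, aversion or allergy, so veterans already active with animals can enrol. The documents do not support treating this as the same defect. Such activity precedes randomisation and is expected equally in both arms. It could dilute or modify the effect, but the formula above does not describe it, and an added exclusion would be a debatable narrowing of the sample. A reader might likewise infer that "a study-specific Previous Experience with Dogs Form" plays no part in the analysis. The article states no use for it, but covariates are commonly left to an analysis plan, which is not at hand.

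**Conclusion.** The point holds as a narrow one. The instruction to control veterans is narrower than the article's own definition of HAI and than the purpose claimed for the control, so full compliance can still put planned animal contact in the control arm. The direction of the effect is toward no difference.

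Its size is unknown. The range of 0.27 to 0.21 SD in place of 0.30 SD assumes that 10% to 30% of controls take up an animal role and gain the full RESCUE effect. With half that effect, the range is 0.285 to 0.255 SD. With no uptake there is no loss. The documents do not show that contamination has occurred, and these figures should not be read as an estimate of it.

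**What to change.** In the Community Involvement volunteer condition, replace the shelter-only sentence with: *Veterans are instructed not to choose any agency or role that involves planned contact with animals.* Have staff check the chosen agency on the weekly Community Involvement Report Form, adding a line for agency and role if the form lacks one. Apply both to remaining enrolment. For controls already enrolled, review the forms on file and describe any animal contact found. No new exclusion criterion or covariate is needed for this point.

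The cost is small. Control veterans lose a little choice, and every handout example named in the article remains available. Because the trial is ongoing, the change needs approval from the institutional review board and the Department of Defense human research office, as the Study/methods monitoring section requires. Earlier and later controls will have had different instructions, so the date of the change should be recorded and reported.

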### Assessment measures

Participants are screened for eligibility by the Project Coordinator who has a master’s degree in counseling psychology. This screening/baseline assessment includes informed consent and administration of a battery of measures consisting of the Clinician Administered PTSD Scale-5 (CAPS [22];), the Structured Clinical Interview for DSM-IV Axis I Disorders (SCID-IV) Modules for Mood and Generalized Anxiety [24]; Clinical Global Impressions (CGI [25];); Digit-Span [26]; and a Medication Tracking Measure. Self-Report measures include the Posttraumatic Stress Disorder Checklist (PCL-5 [27];); Beck Anxiety Inventory (BAI [28];); Patient Health Questionnaire (PHQ-9 [29];); Quality of Life Index (QLI [30];); World Health Organization Disability Assessment Schedule II (WHODAS II [31];; Emotional Reactivity and Numbing Scale (ENRS [32];); a study-specific Previous Experience with Dogs Form; Deployment Risk and Resilience Inventory (DRRI-2 [33];). The baseline assessment typically occurs over one to two sessions and veterans are compensated US$50.00 for their time.

Weekly treatment session measures include the PCL-5; Utilization of Treatment Inventory (UTI, weekly [21];), a study-specific Community Involvement Report Form, and a study-specific Violations of Expectancies about Imaginal Exposure Form (VEMIE; sessions 2, 3, and 4). At mid-treatment veterans complete the BAI; PHQ-9; Medication Tracking Measure; and Client Satisfaction Questionnaire – 8 (CSQ-8 [34];).

At post treatment and 3 months, veterans complete the same battery of instruments as those administered during the baseline minus the SCID-IV, Treatment Expectancies Form, and Previous Experience with Dogs Form. The 3-month battery does not include a thematic interview. Mid-treatment and post-treatment follow-up assessments typically occur over one session and veterans are compensated US$50.00 for each assessment completed (i.e., mid-treatment, post-treatment, and 3-month follow-up). Veterans who drop out of treatment prematurely are encouraged to complete the follow-up assessments and are likewise eligible for compensation. All assessments, including the baseline, are conducted by master’s level or above personnel trained in the interview procedures by the PI. Additionally, all assessors participated at the onset of the study in a formal CAPS training provided by a senior clinician in the Charleston PCT clinic. All post assessments are conducted by a study personnel blind to randomization status.

### Thematic interview

As part of the post-treatment assessment, veterans complete a 30–45-min individual thematic interview designed to get their impression of the treatment program overall, their perceptions regarding their current functioning and symptoms relative to the start of treatment, any difficulties/barriers they faced with any aspect of the program, and their thoughts about specific components of PE (i.e., imaginal and in vivo) and their volunteer assignment. Aside from gathering information to potentially improve the program moving forward, it is anticipated that the thematic interview will provide a better understanding of if, and how, HAI and the control volunteer assignment impacted veterans with regard to their symptoms and/or quality of life.

